| Study Design     | 
This is a single-arm, open-label, multicenter, phase 2 clinical study. The 83 patients with advanced NSCLC who have progressed after at least one line standard of care will be enrolled in the study. The aim of the study is to evaluate the efficacy and safety of HA121-28 tablets in patients with unresectable locally advanced or metastatic RET fusion-positive NSCLC.
 
After obtaining informed consent from the patients or their guardians, patients will be screened within 28 days prior to administering the study treatment.
 
Eligible patients will receive HA121-28 tablets at a recommended starting dose of 450 mg once daily for 21 consecutive days, followed by a 7-day drug-free period, constituting a 28-day treatment cycle. The treatment will be continued until disease progression, intolerable toxicity, death, or any other reason for interruption of the treatment. During the treatment period, investigators can adjust the dose based on tolerability. Refer to Section 6.1.3 for the dose adjustment. Safety assessments will be conducted every cycle on day 28 (<math>\pm 3</math> days). Tumor assessments will be performed using computed tomography/magnetic resonance imaging (CT/MRI) according to RECIST 1.1 every 8 weeks (<math>\pm 7</math> days) for the first 40 weeks and then every 12 weeks (<math>\pm 7</math> days) thereafter until disease progression, initiation of new anti-tumor therapy, death, or patient withdrawal from the study (whichever occurs first).
 
For patients who discontinue treatment and/or withdraw from the study during the study period, an end-of-treatment/withdrawal visit should be conducted within 14 days after the last dose, and a safety follow-up visit should be conducted on day 28 after the last dose. Patients will be given telephone or on-site visits every 12 weeks (<math>\pm 7</math> days) after completing the last tumor assessment to determine their survival status and subsequent anti-tumor therapy.
 |

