| 
Note: All examinations scheduled in this study are mandatory requirements for the clinical study. If the investigator has a reasonable clinical need, they may add relevant examination items and frequency during the study period. All patients must sign an informed consent form before any study-related procedures are performed. For reasonable clinical needs, retesting is allowed during the screening period, and the final examination result before enrollment will be used to determine the inclusion/exclusion criteria. For patients who have already signed the informed consent form, re-screening is allowed for reasonable reasons.
 
[1] The 12-lead electrocardiogram examination on day 15 of cycle 1 conducted at an external hospital will be allowed.
 
[2] If the study treatment is discontinued for ≥7 days for any reason during the treatment period, the patient will resume the drug upon recovery and proceed directly to the next cycle.
 
[3] If the treatment has ended/the patient has withdrawn from the study, and the assessments conducted during the end-of-treatment visit overlap with the safety assessments conducted during the previous visits, there is no need to repeat the assessments.
 
[4] Demographic data: gender, date of birth, age, ethnicity.
 
[5] Height/weight: Height and weight will be measured during the screening period, and only weight will be measured during subsequent visits.
 
[6] Tumor history and treatment history: Collect information on pathological diagnosis time, clinical stage, pathological type, presence of brain metastasis, etc. Also collect information on previous tumor treatment history, radiotherapy history, surgical treatment history, and previous treatment outcomes. Additionally, collect information on RET gene fusion.
 
[7] Collection of tumor tissue samples or blood: This is an optional requirement. Patients may provide previous genetic testing reports for the sponsor's review and confirmation. For those who do not meet the requirements or do not have previous genetic testing reports, sufficient tumor tissue samples (at least 5 slices) and 2ml peripheral blood control samples need to be provided during the screening period. If it is difficult to obtain tumor tissue samples, blood samples (8-10 ml) can also be accepted for RET gene testing. The sample and operational requirements for genetic testing are detailed in the "Central Laboratory Operation Manual".
 
[8] Personal and medical history: Patient's smoking and quitting history, medication allergies, medical history or coexisting conditions within the past year.
 
[9] Urinalysis: If the screening period urine protein is ≥++, further quantitative measurement of 24-hour urine protein should be performed. During the treatment period and follow-up period, it may be considered whether to perform further quantitative measurement of 24-hour urine protein
 |   |  |   |                                                                                                                          |   |   |  |   |

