### **4. Study Design**

#### **4.1. Overall Design**

This is a phase 2, single-arm, open-label, multicenter clinical study.

The study plans to enroll 83 patients with advanced NSCLC who have experienced disease progression after at least the first-line standard of care and evaluate the efficacy and safety of HA121-28 tablets in patients with unresectable locally advanced or metastatic RET fusion-positive NSCLC.

After obtaining informed consent from the patients or their guardians, the screening will begin

within 28 days before the patient administering the study treatment.

Eligible patients in screening will enter the treatment period: patients who meet the inclusion criteria will receive HA121-28 tablets at a recommended starting dose of 450 mg once daily for 21 consecutive days, followed by a 7-day drug-free period, constituting a 28-day treatment cycle. Treatment will continue until disease progression, intolerable toxicity, death, or any other reason for discontinuation of treatment. During the treatment period, investigators may adjust the dose based on the patient's tolerance, as detailed in section 6.1.3. Safety assessments will be conducted every cycle on day 28 ( $\pm 3$  days). Tumor imaging assessments will be performed every 8 weeks ( $\pm 7$  days) from C1D1 based on RECIST 1.1 until week 40, and then every 12 weeks ( $\pm 7$  days) thereafter until disease progression, initiation of new anti-tumor therapy, death, or patient withdrawal from the study (whichever occurs first).

Patients who discontinue treatment and/or withdraw from the study should have a treatment completion/withdrawal visit within 14 days of their last dose. A safety follow-up visit should be conducted 28 days after the last dose. After the final tumor imaging evaluation, researchers should contact patients every 12 weeks ( $\pm 7$  days) by phone or in person to determine their survival status and information on subsequent anti-tumor treatment.

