### 6.1.2. Dosing Regimen of Study Treatment

The recommended starting dose is 450 mg. It should be administered once daily for 21 consecutive days, followed by a 7-day drug-free period. Each cycle lasts 28 days and the medication should be taken orally with warm water.

During the treatment period, the investigator may adjust the dosage based on the patient's tolerance.

The time and dose of administration will be recorded in detail in the diary card.

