### **6.4. Compliance with Study Intervention**

At each visit of the patients to the clinic, the investigator and/or authorized personnel from the study site will assess the patient's compliance by counting the pills (number of pills dispensed and returned by the patient), checking the patient's diary card, and reviewing the information provided by the patients and/or their caregiver. The usage record of the study treatment, the dosage taken, and the follow-up interval and completion of the study should be recorded and saved in the drug tracking table or equivalent document.

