## **8.2. Safety and other assessments**

### **Vital signs**

Vital signs include body temperature, respiration, pulse, and blood pressure. It is recommended to rest quietly for at least 3 minutes before measurement and to measure while sitting with the elbow at the same level as the heart. This should be done during the screening period, at the CnD28, EOT visits, and at the visit 28 days after the last medication.

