### **Physical examination**

Physical examination includes skin and mucous membranes, lymph nodes, head and neck, chest, abdomen, spine, musculoskeletal system, nervous system, and other areas. It is conducted during the screening period, CnD28, end of treatment visit, and 28 days after the last dose of medication.

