### Laboratory tests

Serology will be performed during the screening period, coagulation function and pregnancy tests will be performed during the screening period and at the end of treatment visit (EOT). Hematology, urinalysis, and blood biochemistry will be performed during the screening period, on Day 28 of Cycle 1, at EOT, and 28 days after the last dose of the study drug. If a patient has previously undergone relevant laboratory tests at the study site and the test results meet the protocol requirements, the patient does not need to undergo the tests again and the results prior to signing the informed consent form will be used to determine eligibility. Please refer to Table 8-1 for specific parameters of each test.

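### Section 8.2 schedules on-treatment laboratory tests only on Day 28 of Cycle 1, contradicting the per-cycle testing required elsewhere in the protocol

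*Protocol*

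**What the plan says.** Three places in the protocol set per-cycle safety testing.

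- Section 1.1 (Study Design): "Safety assessments will be conducted every cycle on day 28 ( \pm 3 days").
- Section 4.1 repeats it: "Safety assessments will be conducted every cycle on day 28", with the same window.
- The Schedule of Assessment (Section 1.2) marks haematology, blood chemistry and urinalysis in the CnD28 column, window ±3 days. The note beneath the table makes every scheduled examination mandatory.

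Section 8.2, which describes each assessment, is split. Three paragraphs agree with the Schedule:

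- Vital signs: "This should be done during the screening period, at the CnD28, EOT visits, and at the visit 28 days after the last medication".
- Physical examination: "It is conducted during the screening period, CnD28, end of treatment visit, and 28 days after the last dose of medication".
- 12-lead ECG: screening, C1D15, CnD28, EOT and the visit 28 days after the last dose.

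The laboratory paragraph does not: "Hematology, urinalysis, and blood biochemistry will be performed during the screening period, on Day 28 of Cycle 1, at EOT", followed by the visit 28 days after the last dose. Its only on-treatment time point is in Cycle 1.

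**The concern.** Section 8.2 is the text a site reads to learn what each test involves and when to do it. For laboratory tests it gives a different schedule from the table, the synopsis and Section 4.1.

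Several rules in Table 6-2 depend on a laboratory result. Grade 2 ALT/AST starts weekly liver tests; Grade 3 means a hold; Grade 4, or ALT/AST above 3×ULN with bilirubin above 2×ULN, means stopping. Grade 3 haematological toxicity means a hold and Grade 4 means stopping. These abnormalities can be silent, and Section 2.3.1 lists raised ALT and serum creatinine among the main adverse reactions. The weekly liver monitoring begins only once an abnormality has been found, so it cannot replace the routine check that finds it.

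A site that took the laboratory paragraph at its word would have no scheduled result to set against these rules from Cycle 2 until end of treatment. The before-and-after laboratory summaries in Section 9.4.6 would also have fewer on-treatment values from that site.

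**Working it through.** **Inputs**

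- Cycle: 21 dosing days, then "followed by a 7-day drug-free period. Each cycle lasts 28 days" (Section 6.1.2).
- Schedule of Assessment: haematology, chemistry and urinalysis at CnD28 (Section 1.2).
- Section 8.2: the same tests on treatment at Day 28 of Cycle 1 only.

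**Step 1. The texts side by side**

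| Place | On-treatment timing | Applies to laboratory tests? |
|---|---|---|
| 1.1 Summary, Study Design | every cycle, Day 28 ±3 | yes, as safety assessments |
| 4.1 Overall Design | every cycle, Day 28 ±3 | yes, as safety assessments |
| 1.2 Schedule of Assessment | CnD28 ±3, mandatory | yes, marked test by test |
| 8.2 Vital signs | CnD28 | no |
| 8.2 Physical examination | CnD28 | no |
| 8.2 12-lead ECG | C1D15 and CnD28 | no |
| 8.2 Laboratory tests | Day 28 of Cycle 1 | yes |

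The laboratory paragraph stands alone. It differs from the three places that also govern these tests and from its three neighbours in Section 8.2. Nothing in the protocol gives a reason to stop routine laboratory tests after Cycle 1. The likely explanation is that Cycle n became Cycle 1.

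**Step 2. Size of the difference if Section 8.2 is followed literally**

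Take a patient treated without interruption to week 40. Week 40 is only a convenient marker; it is where imaging moves from every 8 to every 12 weeks.

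- Days: 40 × 7 = 280.
- Cycles: 280 / 28 = 10.
- CnD28 laboratory checks under the Schedule: 10.
- On-treatment checks under the Section 8.2 paragraph: 1.
- Difference: 10 − 1 = 9, in Cycles 2 to 10.
- Planned doses in those cycles: 9 × 21 = 189.

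These figures describe a literal reading of one paragraph. They do not describe what the protocol as a whole requires, which is 10 checks.

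**Step 3. Which rules are touched**

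The ALT/AST, bilirubin and haematological rows of Table 6-2 depend on the affected tests. The QTc row does not, because the ECG paragraph keeps CnD28. The skin and diarrhoea rows rest on clinical findings.

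**Step 4. Bearing on the primary analysis**

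The stated design reproduces: with 83 patients and success at 34 or more responses, the exact type I error at 30% is 0.0218, the exact power at 45% is 0.8018, and the Clopper-Pearson interval for 34/83 is 30.28% to 52.31%. None of these uses the laboratory schedule.

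**The case against.** The best defence is that the protocol already answers the question. The Schedule marks the tests at CnD28, its note makes them mandatory, and Sections 1.1 and 4.1 say every cycle. A site that skipped the tests in Cycle 2 would breach a mandatory schedule. Investigators may also add tests, and Table 6-2 brings in weekly liver tests once ALT/AST reaches Grade 2. On this view the point is a one-word correction.

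Most of that stands, and it limits the point to an inconsistency. A reader might infer that patients go unmonitored from Cycle 2 on, with 189 doses unchecked by week 40. The documents do not support that: it needs a site to follow one paragraph against all the others. What remains is that the paragraph is wrong as written, and no sentence says which text prevails.

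A reader might also infer a second gap. The visit window runs to Day 31, and no rule makes the next cycle's first dose wait for the CnD28 results. Footnote [2] of the Schedule covers only longer breaks: "If the study treatment is discontinued for ≥7 days for any reason during the treatment period, the patient will resume the drug upon recovery". If dosing restarted by calendar on Day 29 with tablets in hand, visits on Days 29, 30 and 31 would follow 1, 2 and 3 new doses if that day's tablet came before the visit, or 0, 1 and 2 if it came after.

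The documents do not support this as an error. Day 29 is not written anywhere, and no text tells patients to restart before review. Section 6.4 has staff count the "number of pills dispensed and returned by the patient" but sets no dispensing interval; if tablets are handed out only at the visit, the count is 0. A hard rule would delay treatment in patients with no toxicity. Leaving the decision to the investigator, as Section 6.1.3 does, is a defensible choice.

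**Conclusion.** The contradiction is real, and its severity is minor. The laboratory paragraph of Section 8.2 states a safety-monitoring schedule that conflicts with Sections 1.1, 1.2 and 4.1 and with its own neighbouring paragraphs. It is probably a slip.

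The effect is conditional. If every site works from the Schedule, nothing is lost. If a site works from Section 8.2 alone, it does 1 scheduled on-treatment laboratory check where 10 are intended by week 40, assuming uninterrupted 28-day cycles and no added tests. The documents give no basis for estimating how many sites would do so, or how often a silent abnormality would be missed.

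The conclusion rests on reading CnD28 as every cycle, which the wording of Sections 1.1 and 4.1 confirms. It does not extend to the timing of the next cycle's first dose.

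**What to change.** In the laboratory paragraph of Section 8.2, replace the reference to Day 28 of Cycle 1 with: Day 28 of each cycle (CnD28, ±3 days). Leave the other time points in that paragraph, the Schedule of Assessment, the visit window and Table 6-2 as they are.

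The cost is one phrase in the next amendment. No visit, sample or test is added beyond what the Schedule already requires. Until the amendment is in force, a short note to sites that the Schedule governs would serve the same purpose. No rule tying dosing to the CnD28 results is proposed.

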## 1.2. Schedule of Assessment

| Test Period                                                            | Screening |       | Treatment Period |          |          | End of
Treatment/Withdrawal Visit
(EOT) [3] | Safety Follow-up Period    | Follow-
up     |
|------------------------------------------------------------------------|-----------|-------|------------------|----------|----------|---------------------------------------------------|----------------------------|-------------------|
| Visit time                                                             | -28~-1    | -7~-1 | C1D1             | C1D15[1] | CnD28[2] | Within 14 days of the last
dose                | Day 28 after the last dose | Every 12
weeks |
| Window                                                                 | N/A       | N/A   | N/A              | ± 1 day  | ± 3 days | N/A                                               | ± 3 days                   | ± 7 days          |
| Informed Consent                                                       | ×         |       |                  |          |          |                                                   |                            |                   |
| Demographic data [4]                                                   | ×         |       |                  |          |          |                                                   |                            |                   |
| Height/Weight [5]                                                      | ×         |       |                  |          | ×        | ×                                                 |                            |                   |
| Tumor History and Treatment
History [6]                             | ×         |       |                  |          |          |                                                   |                            |                   |
| Tumor tissue samples or blood
collection [7]                        | ×         |       |                  |          |          |                                                   |                            |                   |
| Personal and other past medical
history or concomitant diseases [8] | ×         |       |                  |          |          |                                                   |                            |                   |
| Physical examination                                                   | ×         |       |                  |          | ×        | ×                                                 | ×                          |                   |
| ECOG performance score                                                 | ×         |       |                  |          | ×        | ×                                                 |                            |                   |
| Vital signs                                                            |           | ×     |                  |          | ×        | ×                                                 | ×                          |                   |
| Hematology                                                             |           | ×     |                  |          | ×        | ×                                                 | ×                          |                   |
| Blood chemistry                                                        |           | ×     |                  |          | ×        | ×                                                 | ×                          |                   |
| Urinalysis [9]                                                         |           | ×     |                  |          | ×        | ×                                                 | ×                          |                   |
| Coagulation                                                            |           | ×     |                  |          |          | ×                                                 |                            |                   |
| Serum virology                                                         | ×         |       |                  |          |          |                                                   |                            |                   |
| Pregnancy test [10]                                                    |           | ×     |                  |          |          | ×                                                 |                            |                   |
| 12-lead ECG [11]                                                       |           | ×     |                  | ×        | ×        | ×                                                 | ×                          |                   |
| Echocardiography                                                       | ×         |       |                  |          |          | ×                                                 |                            |                   |

|                                                                                                                                                                                                                                                                                                                                                                                                                                                                                                                                                                                                                                                                                                                                                                                                                                                                                                                                                                                                                                                                                                                                                                                                                                                                                                                                                                                                                                                                                                                                                                                                                                                                                                                                                                                                                                                                                                                                                                                                                                                                                                                                                                                                                                                                                                                                                                                                                                                                                                                                                                                                                                                                                                                                                                                                                                                                                                                                                                                                                                             |   |  |   |                                                                                                                          |   |   |  |   |
|---------------------------------------------------------------------------------------------------------------------------------------------------------------------------------------------------------------------------------------------------------------------------------------------------------------------------------------------------------------------------------------------------------------------------------------------------------------------------------------------------------------------------------------------------------------------------------------------------------------------------------------------------------------------------------------------------------------------------------------------------------------------------------------------------------------------------------------------------------------------------------------------------------------------------------------------------------------------------------------------------------------------------------------------------------------------------------------------------------------------------------------------------------------------------------------------------------------------------------------------------------------------------------------------------------------------------------------------------------------------------------------------------------------------------------------------------------------------------------------------------------------------------------------------------------------------------------------------------------------------------------------------------------------------------------------------------------------------------------------------------------------------------------------------------------------------------------------------------------------------------------------------------------------------------------------------------------------------------------------------------------------------------------------------------------------------------------------------------------------------------------------------------------------------------------------------------------------------------------------------------------------------------------------------------------------------------------------------------------------------------------------------------------------------------------------------------------------------------------------------------------------------------------------------------------------------------------------------------------------------------------------------------------------------------------------------------------------------------------------------------------------------------------------------------------------------------------------------------------------------------------------------------------------------------------------------------------------------------------------------------------------------------------------------|---|--|---|--------------------------------------------------------------------------------------------------------------------------|---|---|--|---|
| PK blood sampling                                                                                                                                                                                                                                                                                                                                                                                                                                                                                                                                                                                                                                                                                                                                                                                                                                                                                                                                                                                                                                                                                                                                                                                                                                                                                                                                                                                                                                                                                                                                                                                                                                                                                                                                                                                                                                                                                                                                                                                                                                                                                                                                                                                                                                                                                                                                                                                                                                                                                                                                                                                                                                                                                                                                                                                                                                                                                                                                                                                                            |   |  | × | ×                                                                                                                        | × | × |  |   |
| Tumor Imaging Assessments                                                                                                                                                                                                                                                                                                                                                                                                                                                                                                                                                                                                                                                                                                                                                                                                                                                                                                                                                                                                                                                                                                                                                                                                                                                                                                                                                                                                                                                                                                                                                                                                                                                                                                                                                                                                                                                                                                                                                                                                                                                                                                                                                                                                                                                                                                                                                                                                                                                                                                                                                                                                                                                                                                                                                                                                                                                                                                                                                                                                    | × |  |   | Every 8 weeks ± 7 days from Week 1 to Week 40, and every 12 weeks ± 7 days thereafter, relative to Cycle 1 Day 1. |   |   |  |   |
| Concomitant Medications/Treatments                                                                                                                                                                                                                                                                                                                                                                                                                                                                                                                                                                                                                                                                                                                                                                                                                                                                                                                                                                                                                                                                                                                                                                                                                                                                                                                                                                                                                                                                                                                                                                                                                                                                                                                                                                                                                                                                                                                                                                                                                                                                                                                                                                                                                                                                                                                                                                                                                                                                                                                                                                                                                                                                                                                                                                                                                                                                                                                                                                                           |   |  |   |                                                                                                                          |   | × |  |   |
